### Study aims

The primary aim of the current study is to investigate the feasibility and acceptability of conducting Signposts with videoconferencing as the mode of clinician support. In particular, this study intends to investigate this in families where the child sustained the TBI in early childhood, an age group that may be particularly prone to post-TBI poor outcomes [35–37] but, to date, has been relatively neglected with minimal attention directed to development of age-appropriate evidence-based interventions targeting behaviour problems.

More specifically, the study objectives are to:Investigate the feasibility of delivering the programme with clinician support via videoconferencing, with the goal of developing a larger RCT. This will be investigated with the collection of data on sample retention rates, participant programme adherence, and duration to reach target sample size.Collect information to inform on the clinical practicality of delivery through this medium, including the duration of videoconference sessions, rate of technology difficulties that cause disruption to sessions, and the time frame for programme completion (in weeks).Explore the acceptability of the programme when delivered through this medium, with completion of a consumer satisfaction survey, as well as by enquiring on the participant’s comfort with using the technology. It is expected that, consistent with programme delivery through different modalities, the programme will have a high level of consumer satisfaction in this population when delivered with clinician support via videoconferencing.Explore preliminary clinical outcomes across those who completed the programme compared with those on a wait-list, in order to inform likely efficacy estimates for a fully powered RCT. Primary measures will assess child behaviour, while secondary outcome measures will assess parent distress, parenting disciplinary style, parenting sense of competency, and family functioning. These will be measured using questionnaires considered standard for research involving the Signposts programme (see, for example, Woods and colleagues [23]). It is expected that those who complete Signposts will report reductions in post-TBI child behaviour problems, parental distress, and dysfunctional parenting, while increasing family functioning and parental sense of competency.

## Methods/design

### Overall study design

The current pilot study employs a two-arm, parallel non-randomised design, in which a treatment as usual wait-list group is compared with a group in which the ‘Signposts’ programme is completed with clinician support via videoconferencing (see Fig. 1). The wait-list group may access any therapies or treatments considered standard treatment for a paediatric TBI.

**Fig. 1 Fig1:**
[figure not shown]
Participant flow diagram

Data will be collected at four time points: (i) pre-injury functioning at the time of enrolment in the study and then (ii) pre-intervention, (iii) immediately post-intervention, and (iv) at the 4-month follow-up post-intervention. Data collected from those who complete the intervention will be compared with data collected at equivalent time points from a wait-list control group. This study has been granted ethics approval by the Human Research Ethics Committee of the Royal Children’s Hospital, Melbourne.

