**Methods/design:**

The sample for this feasibility study will be recruited from the Royal Children’s Hospital, Melbourne, and the Victorian Paediatric Rehabilitation Service. Participants will be the parents of a child who sustained a TBI between the ages of 2.0 and 6.11, within the previous 2 years. The parents of 15 children will complete the programme, with clinician support via videoconferencing, while the parents of a further 15 children will form a treatment as usual wait-list control group. Parents complete questionnaires assessing their child’s behaviour, as well as assessing their own mental health, sense of parenting competency, disciplinary style, and family functioning. These will be completed upon enrolment in the study regarding their child’s pre-injury behaviour and then again pre-intervention, immediately post-intervention, and 4 months post-intervention. Parents who complete the intervention will also complete questionnaires assessing their satisfaction with the programme and its delivery. Information will be collected on the feasibility, clinical practicality, and acceptability of the programme when delivered through this medium.

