#### Data collection

Data will be recorded to capture the number of eligible parents approached, the number who consented to the programme, and the number who successfully completed the programme, as well as reasons for non-participation and non-completion.

Questionnaires will be administered using a secure online data collection instrument (RedCap), with parents sent web links at the appropriate time points. Upon enrolment in the study, parents will be sent the web-link questionnaires and asked to complete the outcome measure questionnaires retrospectively, reporting on their child and family’s functioning prior to the TBI. It is acknowledged that this may be vulnerable to parent reporting bias, particularly where children are several years post-injury. However, evidence suggests that post-TBI behavioural problems may not emerge or present for intervention until several years post-injury [10, 11], which means that including families several years post-injury more closely mirrors the clinical setting. It therefore seems reasonable to include such families in this feasibility study. Future research may aim to minimise this bias by reducing the eligible time since injury.

Prior to commencing the programme, approximately 1 month following initial questionnaire completion, parents will be asked to complete the measures again with regard to their family and child’s *current* functioning. Outcome questionnaires will again be sent in the form of web links via email immediately after the intervention and 4 months post-intervention. The approximate timeline for completion of these questionnaires is summarised in Table 2.

**Table 2 Tab2:** Summary of measures used

Construct	Measure	Time point			
		1	2	3	4
Socioeconomic status	Social Risk Index	●			
Outcome measures					
Child behavioural outcomes	Child Behavior Checklist	●	●	●	●
Family outcomes	McMaster Family Assessment Device	●	●	●	●
Parental functioning					
Parental psychological distress	Depression Anxiety Stress Scales	●	●	●	●
Confidence and satisfaction in the parenting role	Parenting Sense of Competence Scale	●	●	●	●
Disciplinary practices	Parenting Scale	●	●	●	●
Programme satisfaction	Consumer Satisfaction Scale			●^a^	

Time point 1 = retrospectively completed about pre-injury behaviour, 2 = pre-intervention, 3 = post-intervention, 4 = 4 months post-intervention

^a^Intervention group only

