6	Complete homework for module 5 prior to videoconference	Videoconference #3 Homework reviewed for module 5
7	Read module 6 Begin homework	
8	Complete homework for module 6 prior to videoconference	Videoconference #4 Homework reviewed for module 6
9	Read module 7 Begin homework	
10	Complete homework for module 7 prior to videoconference	Videoconference #5 Homework reviewed for module 7
11	Complete post-intervention questionnaires Return iPad	

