### Sample size

The current feasibility study sample will aim to consist of 15 parents who will participate in the intervention and a further 15 allocated to the wait-list control group. Studies also exploring the feasibility of family-centred behaviour interventions in this population used similar sample sizes [49–52] and detected promising preliminary results. With recruitment in this population frequently difficult and slow, we aim to measure the duration of time taken to recruit this sample in order to guide estimates of recruitment duration for a larger RCT.

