### Data analysis

Frequencies and percentages will be used to describe the population across key demographic and injury variables. We will compare the intervention and wait-list control groups across key variables (age at injury, injury severity, social risk, pre-injury behaviour, and pre-intervention behaviour) to detect any significant difference which may later compromise the generalisation of the findings.

Investigating the feasibility, clinical practicality, and acceptability of Signposts with videoconferencing support will be exploratory in nature. The objective is to collect information on ease of use, participant satisfaction, homework completion rates, programme completion and adherence, and attrition rates. Rates of programme attrition will be reported, as well as consumer satisfaction with the programme (reported as mean scores and percentages for items on the CSS).

To examine preliminary data on the impact of the programme on key outcome areas, we will compare the post-intervention scores on the CBCL scales, FAD, DASS, PS, and PSOC across the intervention and control groups and will report the mean and standard deviation of each group across these measures. To report preliminary findings on the maintenance of any treatment effects, means and standard deviations will be reported to assess any change within the intervention group from post-intervention to 4-month follow-up across the CBCL scales, FAD, DASS, PS, and PSOC. These findings may inform efficacy estimates for a larger RCT.

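### The clinical-outcome comparison sets programme completers against the wait-list group, a condition applied after allocation to one arm only, and the analysis section does not settle who is analysed

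*Protocol article*

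**What the plan says.** Three places in the protocol article describe the clinical-outcome comparison.

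- Overall study design, in the text after Figure 1: "Data collected from those who complete the intervention will be compared with data collected at equivalent time points from a wait-list control group".
- Study aims, fourth objective, which looks ahead to a fully powered trial: "Explore preliminary clinical outcomes across those who completed the programme compared with those on a wait-list, in order to inform likely efficacy estimates". The hypothesis that follows is also framed around parents who complete Signposts.
- Data analysis: "we will compare the post-intervention scores on the CBCL scales, FAD, DASS, PS, and PSOC across the intervention and control groups". This names the groups but does not say whether the intervention group means everyone allocated or only those who finished.

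On timing, the Data collection section says: "Outcome questionnaires will again be sent in the form of web links via email immediately after the intervention and 4 months post-intervention". Table 3, presented as an approximate timeline, has the entry "Complete post-intervention questionnaires" at week 11, after the fifth videoconference. Weeks to programme completion is itself listed as an outcome in the Study aims.

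On the target, the abstract says "The parents of 15 children will complete the programme", whereas the Sample size section gives "15 parents who will participate in the intervention and a further 15 allocated to the wait-list control group".

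**The concern.** Completing the programme is something a family does after allocation. Only intervention families can meet or fail the condition, because the wait-list has no programme to finish. If families who stop differ in child behaviour, parental distress or response, removing them changes the mean of one arm and leaves the other as it was. Comparing completers with the wait-list then mixes any programme effect with the difference between families who persist and families who do not.

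Non-completion is expected: the Data collection section plans to count completers and record reasons for stopping. The Background links parental distress to child behaviour problems and to less positive parenting, so it is reasonable to worry that those who stop are not a random subset. A larger pilot would not remove this bias. The estimate is also meant to be carried forward, since both the Study aims and the Data analysis section say it may inform efficacy estimates for a larger trial. An inflated pilot effect leads to a trial that is too small.

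**Working it through.** **Reproducing the plan's figure.** The 15 + 15 is justified by the size of similar feasibility studies. No alpha, power, effect size or dropout rate is given, so there is nothing to reproduce.

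**Inputs.** SD = 10 is the T-score SD given under Child behavioural outcomes; the SD in this sample may differ. The group size of 15 comes from the Sample size section. The non-completion fraction d and the correlation r between the tendency to stop and a worse score are my assumptions. The true effect is set to zero to isolate the selection term.

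**Model.** Completion is governed by a latent normal variable with correlation r to the worse outcome, and the fraction d with the strongest tendency to stop is lost from the intervention arm only. With z = Φ⁻¹(1 − d), the completer mean moves towards better scores by

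shift = r × SD × φ(z) / (1 − d).

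| d | z | φ(z) | r = −0.3 | r = 0 | r = 0.3 | r = 0.5 |
|---|---|---|---|---|---|---|
| 20% | 0.842 | 0.280 | −1.05 | 0 | 1.05 | 1.75 |
| 30% | 0.524 | 0.348 | −1.49 | 0 | 1.49 | 2.48 |
| 40% | 0.253 | 0.386 | −1.93 | 0 | 1.93 | 3.22 |

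Positive values, in T points, favour the programme. For r from 0.3 to 0.5 the range is about 1.0 to 3.2 points, or 0.10 to 0.32 SD.

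**Against the pilot's precision.** With 15 per group the standard error of the difference is 10 × √(2/15) = 3.65, about 3.7 points. With 12 completers (d = 20%) it is 10 × √(1/12 + 1/15) = 3.87, and with 9 (d = 40%) it is 10 × √(1/9 + 1/15) = 4.22. Every shift in the table is below one standard error.

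**What it could do to the next trial.** Suppose the true effect is 0.40 SD and the trial is planned for 80% power at two-sided 5%. The size per arm is 2 × (1.960 + 0.842)² / 0.40², which rounds up to 99. A planning effect inflated by 0.10 SD (to 0.50) gives 63 per arm, with actual power of 61%. Inflated by 0.15 SD (to 0.55), it gives 52 per arm and 53%. This shows only the selection term; random error in a pilot of this size can be larger.

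**The target.** If 15 meant completers, 20% non-completion would require 15 / 0.8 = 18.75, so 19 starters. If it means participants, 15 start.

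**The case against.** The strongest reply is that the section specifying the analysis compares groups, not completers, and that the completer wording comes from the aims and the design overview. That shows an inconsistency. It does not lift a restriction that appears in the objective, the hypothesis and the design section.

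Other parts of the reply stand.

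- A reader might infer that questionnaires are triggered by finishing, so that a parent who stops is never assessed. The Data collection section does not exclude such parents, and Table 3 gives a scheduled week.
- A reader might infer that slow finishers are assessed later than controls. The design section says control data come from equivalent time points; how these are matched is detail an article may leave to the full protocol.
- A reader might say that dropout affects one arm only. Wait-list parents can also fail to return questionnaires; only the completion rule is one-sided.
- A reader might fear that the attrition denominator is lost. The Data collection section records numbers approached, consented and completed, so attrition can be calculated however the 15 is read.
- The direction is not established. The Background ties distress to parenting style, not to stopping the programme, and no dropout rate is given.

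Finally, the primary aim is feasibility and acceptability, and the outcomes are exploratory and reported as means and standard deviations with no declared efficacy test. That limits the severity but leaves the planned use of the estimate untouched.

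**Conclusion.** The concern holds at moderate severity. As described in the aims and the design section, the comparison conditions the intervention arm on completion and places no matching condition on the wait-list, and the Data analysis section leaves the matter open. The 1.0 to 3.2 point range depends on the assumed non-completion, the assumed correlation and an SD of 10. The documents do not support saying that the bias certainly favours the programme, or that its size is known.

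The mismatch over the 15 families sets abstract wording against the sample size section and needs only aligning. It should not be read as showing that recruitment is planned four families short.

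Two limits remain whatever is changed here. Allocation is non-random, alternating by date of injury, and it takes place before invitation and consent. A set of all consented parents is therefore itself formed after allocation. It avoids the further selection on completion but does not make the groups exchangeable.

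**What to change.** - In the Study aims, Overall study design and Data analysis sections, define the main comparison as all consented parents in the group to which they were allocated, whether or not they finish the programme.
- Send the time-point-3 and time-point-4 web links to both arms, including parents who stop early, at fixed intervals from time point 2. Table 3 already lists week 11 for time point 3, counted from the pre-intervention interview. The wait-list has no programme to start, so the time-point-2 questionnaire is the natural common anchor.
- Report completers only as a labelled supplementary description.
- Use one description of the 15 intervention families in the abstract and the Sample size section.

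The cost is wording, plus links sent on a calendar date instead of at the end of the programme. The drawback is that some slow finishers would be assessed before their last session, which the report should state. The questionnaire schedule is best settled before data collection, because outcomes not collected at the time from parents who stop cannot be recovered afterwards.

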### Participants

Participants are the primary caregivers (herein referred to as parents) of at least one child who has sustained a TBI within the prior 2 years. Children aged 2.0–6.11 at the time of injury, who sustained mild, moderate, or severe injuries, will be eligible to participate.

Inclusion criteria for the current study are that medical records suggest that parents and children have sufficient English skills, that the child has no prior history of neurological or developmental disorder, no diagnosed severe psychiatric disorder in the parent, and no documented evidence that the TBI was non-accidental.

In keeping with previous research [38], TBI will be classified by injury severity (mild, moderate, or severe). For young children, these categories are largely based on scores on the Paediatric Glasgow Coma Scale (GCS) [39], which provides ratings of the depth and/or duration of altered consciousness post-injury. As an adaptation to the initial scale devised for use in adults [40], GCS is instead rated in young children by recording behavioural rather than verbal responses. Scores are assigned on a scale of 3–15, where 3 indicates no verbal, motor, or visual responsiveness to stimuli, and 15 indicates full responsiveness.

Classifications of injury severity are made according to the following criteria:(i)Mild: GCS 13–15, no evidence of mass lesion on CT/MRI and no neurological deficits(ii)Moderate: GCS 9–12, mass lesion or other evidence of specific injury on CT/MRI and/or neurological impairment(iii)Severe: GCS 3–8, mass lesion or other evidence of specific injury on CT/MRI and/or neurological impairment

### Measures

#### Injury and demographic variables

Injury and medical characteristics of the injured child are obtained, including lowest GCS, length of coma, neuroimaging abnormalities, injury aetiology, family structure, ethnicity, parental education, and parental occupation. Social adversity is calculated based on the Social Risk Index (SRI), which is comprised of six aspects of social status and provides an aggregate score, where a score of 0 or 1 denotes low social adversity, and a score of >2 denotes high social adversity [41].

#### Child behavioural outcomes

The pre-morbid, pre-intervention, and post-intervention behavioural functioning of the children is determined using the Child Behavior Checklist (CBCL) [42]. Two versions of the CBCL will be used. The preschool version of the CBCL is a standardised 100-item questionnaire, which was designed for use on children aged 1.5–5, while the school-aged version is a 113-item questionnaire designed for use on children aged 6–18. The age-appropriate version will be completed by the caregiver regarding their child’s behaviour. The current study used the three summary scores for analysis (total, internalising and externalising behaviour scales). *T* scores are derived for these scales (*M* = 50, SD = 10), where a *T* score greater than or equal to 60 denotes behaviour falling in the clinically significant range.

#### Family outcomes

Family functioning will be assessed with the self-report McMaster Family Assessment Device (FAD) [43, 44]. The 12-item summary scale, FAD-General Functioning (FAD-GF), will be used for analysis. High family dysfunction is indicated by a mean FAD-GF score >2.17 [45].

#### Parental functioning

Parental psychological distress will be measured using the Depression Anxiety Stress Scales (DASS) [46]. The DASS is a 42-item self-report inventory designed to measure the negative emotional states of depression, anxiety, and stress. Symptom levels on each subscale are categorised as falling in the normal, mild, moderate, severe, and extremely severe range according to the criteria outlined in Table 1.

**Table 1 Tab1:** Subscale severity criteria for the DASS

Severity	Depression	Anxiety	Stress
Normal	0–9	0–7	0–14
Mild	10–13	8–9	15–18
Moderate	14–20	10–14	19–25
Severe	21–27	15–19	26–33
Extremely severe	28+	20+	34+

Lovibond and Lovibond [46]

The total for each subscale will be used for analysis in the current study.

The Parenting Scale (PS) will be used to measure different styles of disciplinary practices [47]. The PS is a 30-item questionnaire that yields three measures of dysfunctional disciplinary styles in parents: laxness, overreactivity, and verbosity. A total dysfunctional disciplinary style score can be calculated where lower scores reflect better parenting. This score will be used for analysis in the current study.

The Parenting Sense of Competence Scale (PSOC) will be used to measure the parent’s self-reported competency and satisfaction in their parenting [48]. The scale consists of 16 items, from which two dimensions can be derived, reflecting satisfaction with their parenting role and sense of self-efficacy in the parenting role. Total scores across these two dimensions will be used for analysis, with higher scores reflecting greater satisfaction and efficacy.

#### Programme satisfaction

Parent satisfaction with the Signposts programme, and its delivery, will be measured using the nine-item Consumer Satisfaction Scale (CSS), which was developed for the purpose of investigating satisfaction with the Signposts programme [18]. Items on this measure are recorded on a five-point Likert scale, in which participants indicate their level of agreement with a statement about their experience with the programme, from ‘Strongly Disagree’ to ‘Strongly Agree’.

### Procedure

#### Recruitment

Eligible parents are identified by clinicians working in relevant departments at the Royal Children’s Hospital and the Victorian Paediatric Rehabilitation Service in Melbourne. Parents will then be allocated to either the intervention or wait-list control group on an alternating basis according to date of injury.

Recruitment letters will be mailed to parents, introducing the study and inviting them to participate. Parents are provided with information statements and sign the consent form should they wish to participate. Parents who do not accept or decline participation within 2 weeks will be followed up with a phone call.

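### Families are allocated by foreseeable alternation on injury date before invitation, consent and both parent-reported baselines, so consent and baseline ratings can differ by arm

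*Protocol article*

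**What the plan says.** All references are to the protocol article.

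- **Recruitment.** The section opens: "Eligible parents are identified by clinicians working in relevant departments". It continues: "Parents will then be allocated to either the intervention or wait-list control group on an alternating basis according to date of injury". Only then does it describe the approach to families: "Recruitment letters will be mailed to parents, introducing the study and inviting them to participate". Consent follows: "Parents are provided with information statements and sign the consent form should they wish to participate". Non-responders are chased: "Parents who do not accept or decline participation within 2 weeks will be followed up with a phone call".
- **Data collection.** Time point 1 comes after consent: "Upon enrolment in the study, parents will be sent the web-link questionnaires". At that point parents are "asked to complete the outcome measure questionnaires retrospectively, reporting on their child and family’s functioning prior to the TBI". Time point 2, on current functioning, follows about one month later and before the programme starts.
- **Overall study design.** The study is openly labelled two-arm, parallel and non-randomised.
- **Data analysis.** The arms are checked for significant differences in age at injury, severity, social risk, pre-injury behaviour and pre-intervention behaviour. Post-intervention scores are then compared between arms. No baseline adjustment is named.
- **Study aims, Data analysis and Sample size.** The between-group results are meant to inform efficacy estimates for a larger trial, and time to recruit is measured "to guide estimates of recruitment duration for a larger RCT".

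**The concern.** Two features combine. The rule is deterministic, so anyone who knows the injury dates and the last assignment can work out the next one. It is also applied before the family is approached, so the arm is already fixed while staff send letters, make follow-up calls and take consent.

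If the arm influences how a family is approached, or whether it agrees, the consented groups can differ in ways that injury date alone would not produce. All the clinical outcome measures are parent-completed questionnaires, so a parent who knows the arm may also rate the child differently at baseline. The Data collection section acknowledges reporting bias only for retrospective recall, not for knowledge of the arm.

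Two outputs for the larger trial are at stake: the between-group estimates, and the time needed to recruit. If families respond to a known arm, recruitment speed reflects uptake of that arm and not willingness to be randomised.

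**Working it through.** **No planned figure to reproduce.** The 15 per arm is justified by similar studies, not by a power calculation. The check has three parts.

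**1. Order of events.** From Recruitment and Data collection: identify → allocate → letter → consent, with a call at two weeks if needed → time point 1 → time point 2 about a month later → programme. Consent and both baselines follow allocation. This rests on the word "then" in the allocation sentence and on the order of the text; the flow diagram (Fig. 1) is not available here.

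**2. What the planned baseline check can detect.** Inputs: n = 15 per arm (Sample size); SD = 10 for CBCL T scores (Child behavioural outcomes); two-sided alpha 0.05 (assumed, as the article gives none).

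- Standard error of a difference: 10 × √(2/15) = 3.65 points.
- 95% confidence interval half-width, normal approximation: 1.96 × 3.65 = 7.2 points.
- Difference detectable with 80% power: (1.96 + 0.84) × 3.65 = 10.2 points, about 1 SD.
- Power from the noncentral t with 28 df and noncentrality d/3.65:

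| True baseline difference d | Power |
|---|---|
| 3 | 13% |
| 5 | 26% |
| 7.5 | 51% |
| 10 | 75% |

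**3. Size of shift from differential consent (illustration, all consent rates assumed).** T scores are taken as N(50, 10), there is no programme effect, and consent in the other arm is unrelated to behaviour.

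*Threshold model.* Consent in one arm differs above and below T = 60, the article's clinical cut-off. The share at or above 60 is 1 − Φ(1) = 0.159. The mean above is 50 + 10 × 0.242/0.159 = 65.2, and the mean below is 50 − 10 × 0.242/0.841 = 47.1. For consent of 80% above and 40% below, the consented mean is (0.8 × 0.159 × 65.2 + 0.4 × 0.841 × 47.1) / (0.8 × 0.159 + 0.4 × 0.841) ≈ 52.1, a shift of 2.1 points. Consent of 70% v 50% gives 0.9, and 80% v 30% gives 3.2.

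*Logistic model.* P(consent) = 1/(1 + exp(0.4 − b·z)), with z the standardised score. Overall consent is 40% to 41%. The slope is b in the programme arm and 0 in the wait-list arm. The shift is 10 × the mean of z among consenters:

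| Slope b | Shift (T points) | Noncentrality (shift/3.65) | Chance the check flags it |
|---|---|---|---|
| 0.25 | 1.5 | 0.40 | 7% |
| 0.50 | 2.8 | 0.77 | 11% |
| 0.75 | 3.9 | 1.08 | 18% |

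*Sensitivity to the flat wait-list slope.* With equal slopes in the two arms the shift is zero. With 0.75 v 0.25 it is 3.9 − 1.5 = 2.4 points.

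**The case against.** The design is declared non-randomised, the primary aim is feasibility and acceptability, and the efficacy results are labelled preliminary. That lowers the stakes. It does not remove bias from estimates that the article wants to carry into an RCT, and the article gives no reason for allocating before invitation.

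Four stronger readings are tempting, and the document does not support them.

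- **Parents consent knowing their arm.** The article does not say that the letter or information statement discloses the arm, or that the arms receive different letters. Knowledge at consent and at time point 1 is an inference. By time point 2, just before the programme starts, it is likely.
- **Alternation by date cannot be kept.** Nothing shows this. Injuries from the prior two years are eligible, so existing cases could be listed and sorted by date first.
- **The bias cannot be separated from a programme effect.** The outcome measures are collected at time points 1 and 2 in both arms, so a shift in measured behaviour would be visible and could be adjusted for. Two limits remain: those scores are themselves collected after allocation, and adjustment does not reach unmeasured differences such as motivation.
- **The feasibility findings as a whole will mislead.** Session length, technology problems, completion time and satisfaction depend little on how families were allocated, and reasons for non-participation are recorded. Recruitment time is the feasibility measure that depends most clearly on the consent process.

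The direction of bias is not fixed either. In the illustration the programme arm starts worse, so an unadjusted post-intervention comparison would understate benefit. The opposite consent pattern would overstate it.

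**Conclusion.** The point stands as a correctable risk, not a demonstrated imbalance. As written, allocation is foreseeable, no concealment is described, and it precedes invitation, consent and both baselines; this part needs no assumption beyond reading the text in sequence. The size does rest on assumptions: about 1 to 4 T points if consent depends on behaviour in one arm only, falling to zero if it depends on behaviour equally in both.

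Whatever the true pattern, a significance check with 15 per arm offers little protection against shifts of a few points, because it has 80% power only at about 10 points. The consequence falls mainly on the preliminary between-group estimates and on recruitment time, and less on the other feasibility measures.

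**What to change.** **Preferred.**

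1. Invite every eligible family with one letter that describes both arms, if the letter does not already do so.
2. Take consent and collect time points 1 and 2.
3. Then allocate from a computer-generated permuted-block list that is concealed from those who identify, call and enrol families.
4. Change the non-randomised label in Overall study design to match.

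**If alternation is kept.** Apply it only after consent and completion of time point 2. Report numbers approached and consenting by arm, which matters for any family whose arm was fixed before invitation. Adjust the between-group comparison for the time point 2 score. The next assignment would still be foreseeable, but the family's consent and baseline ratings would already be on record.

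**Cost.** An ethics amendment and, for the preferred route, a pre-generated list. No extra families or visits are needed, since time point 2 already precedes the programme. Some families may decline if no place is promised, which may lengthen recruitment; that is also information the larger trial needs.
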